## Abstract

**Background:**

Poorly controlled type 2 diabetes mellitus (T2DM) is associated with significant morbidity, mortality and healthcare costs. Control of T2DM can be challenging for healthcare professionals for a number of reasons, including poor concordance with medications, difficulties modifying lifestyle behaviour and also clinical inertia, which is defined as a reluctance among health professionals to intensify medications. A complex intervention, called ComputeriseD dECisIonal support for poorly controlleD typE 2 Diabetes mellitus in Irish General Practice (DECIDE), was developed, identifying T2DM patients with poor glycaemic and blood pressure control and aiming to target clinical inertia, by supporting therapeutic action, including GP-led medication intensification where appropriate. A small-scale, uncontrolled, non-randomised feasibility study highlighted the acceptability of the DECIDE intervention within Irish General Practice. This paper presents a protocol for a pilot cluster randomised controlled trial (RCT) of the DECIDE intervention.

**Methods/Design:**

The pilot cluster RCT will involve 14 practices and 140 patients in Irish General Practice. Intervention GPs will participate in the DECIDE intervention, comprising (a) a training programme for the practices and (b) a web-based clinical decision support system supporting treatment escalation, tailored to specific patient information. Only patients who have poorly controlled T2DM (defined as HbA1c > 70 mmol/mol and/or BP > 150/95) will be included. The primary outcomes will include measures of feasibility such as recruitment and retention of practices and acceptability of the intervention and also HbA1c. Secondary outcomes will include medication intensification, blood pressure and lipids. Control GPs will continue to provide usual care. A process evaluation will be performed to determine whether the intervention is delivered as intended and treatment fidelity assessed to monitor and enhance the reliability and validity of interventions. An exploratory health economic analysis will examine the potential costs and cost effectiveness of the intervention relative to the control.

**Discussion:**

A pilot cluster RCT will establish the feasibility of a complex intervention which aims to support primary care for patients with poorly controlled T2DM in Irish General Practice.

**Trial registration:**

The protocol for the pilot cluster RCT is registered on the ISRCTN Registry at: ISRCTN69498919.

## Background

Over 3.7 million deaths globally were attributable to diabetes in 2012; two thirds of these deaths were caused by the micro- and macro-vascular complications of poorly controlled diabetes [1]. Despite clear evidence to support the management of type 2 diabetes mellitus (T2DM) to prevent its complications, many patients continue to have poor control of glycaemic and cardiovascular risk factors (including blood pressure (BP) and lipids), which are strong surrogate measures of morbidity, mortality, poor quality of life and increased economic burden for patients and health systems [1–4]. Some studies indicate that substantial proportions of patients with T2DM continue to have poor glycaemic and blood pressure control for several years before intensification with therapeutic agents occurs [2, 4, 5].

The reasons for poor control of T2DM are multiple, including a reluctance to intensify medications by a physician, poor adherence and concordance with medications and difficulties modifying lifestyle behaviours [6]. Clinical inertia is one cause of poor control of T2DM and is defined as a failure to apply evidence-based guidance and intensify treatment, and it is an impediment to efficient care [7–9]. The need to intensify therapies in an appropriate and timely manner is a prerequisite to improving the management of T2DM [10–15]. Significant delays in the intensification of oral hypoglycaemic, anti-hypertensive and lipid-lowering medications have been demonstrated [2, 16–20]. The availability of multiple new medications has created a difficulty for physicians, in terms of choice and the complexity of decision-making, with many patients requiring two to three anti-glycaemic medications [3, 21]. A recent network meta-analysis has shown that newer agents such as GLP-1 agonists and SGLT-2 inhibitors are associated with improved mortality [22]. There is also emerging evidence of geographical variations in prescribing anti-diabetic medication, indicating a degree of variation in effective care [23].

### Rationale for the DECIDE study

Assessing glycaemic control over the preceding months, with a HbA1c test, is recommended in all T2DM guidelines, with a lower HbA1c (e.g. below 58 mmol/mol) [3]. Intensive control of glycaemic and cardiac risk factors can reduce mortality, but aggressive reductions in HbA1c, for all patients, may achieve more harm than benefit in certain patient populations [24]. Therefore, targeted reductions in cardiovascular and glycaemic risk factors in certain vulnerable populations (e.g. cognitively impaired) and those with very poorly controlled T2DM have been advocated [25, 26]. A systematic review was performed which sought to understand the effect of healthcare interventions specifically targeting patients with poorly controlled T2DM in primary care and included 38 randomised control trials (RCTs) [26]. It showed that healthcare interventions targeting patients with poorly controlled T2DM have positive, albeit modest, effects on HbA1c with a mean difference (MD) in HbA1c − 3.7 mmol/mol, favouring healthcare interventions over usual care. Interventions targeting those with a higher baseline HbA1c (over 80 mmol/mol) had more beneficial effects (MD − 6.3 mmol/mol). The review suggested that organisational-predominant interventions were more effective than patient-centred interventions, despite patient-related factors being associated with poor control of T2DM. There was only one professional-based intervention, which studied the effect of a patient decision aid [27].

Clinical decision support systems (CDSSs) involve computer software designed to support decision-making, matching individual patient characteristics to a computerised clinical knowledge base and then providing patient-specific assessments or recommendations to the clinician to support a decision that can relate to diagnosis, investigation, prognosis or treatment [28]. Two systematic reviews have previously examined the impact of CDSS on the management of T2DM in primary care—between them looking at 28 trials [29, 30]. They highlighted multi-faceted CDSS interventions with varying results. The first review contained 15 studies, between 2010 and 2012. It found small effects with low quality of evidence. It concluded that there was a need for ‘more potent methods of decision support’ [30]. The different CDSS interventions were too heterogeneous to pool. Only one study by O’Connor et al. involved a CDSS intervention designed to target evidence-based prescribing for general practitioners, but did not focus on those with poor control and also involved practice nurses [30, 31]. The second review contained 20 studies from 1990 to 2011. Processes of case were found to improve in low-risk populations, with the use of CDSS in diabetes management, without clear evidence of improving patient outcomes [29]. None of the CDSS interventions were designed to promote intensification of prescribing in persons with poor glycaemic control [32].

### Development of the DECIDE study and non-randomised feasibility study

We developed a theory-based complex intervention, called DECIDE: ComputeriseD dECisIonal support for poorly controlleD typE 2 Diabetes mellitus in Irish General Practice. The first stage of the UK Medical Research Council (MRC) framework was used to develop the intervention, using the Behaviour Change Wheel (BCW) as a theoretical guide to intervention development [33–35]. The intervention development is reported elsewhere and incorporates a CDSS element, which is professionally targeted at general practitioner (GP) prescribing behaviour, in the treatment of patients with poorly controlled T2DM [36].

We conducted a small-scale, uncontrolled, non-randomised feasibility study to assess the feasibility and acceptability of the DECIDE intervention within Irish General Practice [36]. Table 1 summarises the provision of T2DM healthcare in Ireland. Four GPs, including three academic GPs and one full-time clinical GP, piloted the DECIDE intervention. Each GP applied the intervention process to 15 different patients with poor control of T2DM. All practices were affiliated with the Health Research Board (HRB) Centre for Primary Care Research (http://www.hrbcentreprimarycare.ie). We included all patients who had both HbA1c > 70 mmol/mol and systolic blood pressure (SBP) > 150 mmHg or diastolic blood pressure (DBP) > 95 mmHg. Whilst there is no validated definition of poor control in the literature, we defined it as a HbA1c reading of ≥ 70 mmol/mol and a BP level of ≥ 150/95 mmHg [36]. When this number of patients was < 15, we included a stratified randomised sample of patients with only HbA1c > 70 mmol/mol or SBP > 150 mmHg or DBP > 95 mmHg. The list of 15 patients was kept anonymously within the practice.

**Table 1 Tab1:** Access to healthcare and structure of T2DM care in the Republic of Ireland

Access to general practice healthcare in the Republic of Ireland	
• The General Medical Services (GMS) scheme provides medical care to approximately 40% of the Irish population. It is predominantly means-tested and provides those who are eligible with free general practitioner visits, free hospital care and free medications (except for a prescription levy, currently €2.50 per item to a maximum of €25). A further ~ 5% of the population are entitled to free doctor visits (called a Doctor Visit Card (DVC)) based upon means testing and age-banding (all under-6-year-olds and over-70-year-olds). • The Long Term Illness (LTI) scheme allows persons with certain medical conditions (T2DM being one) to have free access to medications which treat that condition. All patients with type 2 diabetes mellitus (T2DM) can have free medications under the LTI scheme. • The GMS and LTI schemes are administered by the Health Services Executive (HSE) and Primary Care Reimbursement Services (PCRS). • ‘Private patients’ represent approximately 45% of the population and are not entitled to a GMS or DVC card, paying the full cost for attending a GP, out-of-pocket, at the point of healthcare delivery.	
Structure of diabetes care in Republic of Ireland	
• Before October 2015, structured chronic disease management of T2DM was not universally available in Irish primary care. Approximately ten primary care schemes existed in 2013 and 2014, providing different levels of structured T2DM care, often set up as pilot schemes. This represented a maximum of 250 practices within Irish general practice (approximately 10% of total practices). Up until October 2015, the vast majority of structured T2DM care in Ireland was provided in secondary care, through public hospital outpatients or under the care of endocrinologists in private clinics. • In October 2015, a new agreement was reached with GPs entitling all GMS patients to a structured diabetes programme in primary care (called a Diabetes Cycle of Care) with two free GP visits per annum. Private patients with T2DM either pay to receive care from their GP or continue to attend secondary care.	

The non-randomised feasibility study included 15 patients with poor control of T2DM per practice; the sample was generated through a random stratified number of the eligible patients with poor control of either glycaemic and/or BP risk factors. This was performed remotely with no identifiable patient information leaving the practice. The pilot GPs contacted the study team (MM and FB) with the number of persons included in the finder tool report and were informed which 15 patient IDs to include in the pilot study. The finder tool software was developed through a collaboration with the electronic health record (EHR)-vendors and the study team. Each practice was issued with a secure, specific login for the DECIDE website, which housed the CDSS. Approximately one clinical session was spent by pilot GPs performing the DECIDE intervention for all the included 15 patients. Firstly, GPs inserted clinical information for each patient into the DECIDE website, including anonymous baseline information and clinical information necessary for the CDSS (e.g. HbA1c, BP and medications). The second step for each patient involved analysing the suggested treatment intensification options from the CDSS on the DECIDE website. The options were based upon the Irish College of General Practitioners (ICGP) and National Institute for Health and Clinical Excellence (NICE) guidelines, linking the patient’s clinical information and medications to the evidence base for anti-glycaemic, anti-hypertensive and lipid-lowering medications [36]. Choosing an intensification option or acting on a recommendation was at the discretion of each GP.

A total of 37 patients from four practices with ‘poorly controlled’ T2DM received the DECIDE intervention and had complete data for analysis in the practice pilot study. Table 2 summarises the baseline patient’s demographics, highlighting the opportunities to intensify medications. The mean HbA1c was 83.9 mmol/mol, but most patients had mild hypertension (mean 141/83 mmHg) and a normal total cholesterol (mean 4.7 mmol/L). A substantial number of patients were either on no medications or monotherapy for glycaemic and BP management.

**Table 2 Tab2:** Summary of baseline characteristics and medications in the non-randomised feasibility study

Age	56.7 years (13.7) Mean (SD)		
Gender	Male (67%)		
Duration diabetes	7.1 years (5.3) Mean (SD)		
GMS Status	69.2%		
HbA1c level	83.9 mmol/mol (30.8) Mean (SD)		
SBP	140.9 mmHg (22.71) Mean (SD)		
DBP	83.4 mmHg (20.5) Mean (SD)		
Total cholesterol	4.7 mmol/L (1.8) Mean (SD)		
Prevention status	Primary prevention (81%)		
Glycaemic medications (37 patients valid)	No medications	8.1% (*n* = 3)	–
	Monotherapy (without insulin)	32.4% (*n* = 12)	Metformin (*n* = 2)
	Dual therapy (without insulin)	21.6% (*n* = 8)	Metformin + sulphonylurea (*n* = 5) Metformin + DPP-4 inhibitor (*n* = 2) Sulphonylurea + DPP-4 inhibitor (*n* = 1)
	Triple therapy (without insulin)	8.1% (*n* = 3)	Metformin + sulphonylurea + DPP-4 inhibitor (*n* = 3)
	Quadruple therapy (without insulin)	2.7% (*n* = 1)	Metformin + sulphonylurea + DPP-4 inhibitor + SGLT2 inhibitor (*n* = 3)
	Insulin ± other medication(s)	27.0% (*n* = 10)	
Anti-hypertensive medications (37 valid patients)	No medications	24.3% (*n* = 9)	
	Monotherapy	35.1% (*n* = 13)	ACE-inhibitor* (*n* = 11) Beta-blocker (*n* = 2)
	Dual therapy	13.5% (*n* = 5)	ACE-inhibitor + diuretic (*n* = 2) ACE-inhibitor + CCB (*n* = 2) Beta-blocker + CCB (*n* = 1)
	Triple therapy	24.3% (*n* = 9)	ACE-inhibitor + CCB + beta-blocker (*n* = 4) ACE-inhibitor + diuretic + beta-blocker (*n* = 2) ACE-inhibitor + CCB + diuretic (*n* = 1) ACE-inhibitor + CCB + alpha-blocker (*n* = 1) CCB + beta-blocker + ‘Other’ anti-hypertensive (*n* = 1)
	Quadruple therapy	2.7% (*n* = 1)	ACE-inhibitor + CCB + diuretic + diuretic (*n* = 1)
Lipid-lowering medications (37 valid patients)	No medication	27% (*n* = 10)	
	Monotherapy	70.3% (*n* = 26)	Statin (*n* = 23) Ezetamibe (*n* = 2) Fibrate (*n* = 1)
	Dual therapy	2.7% (*n* = 1)	Statin + fibrate (*n* = 1)

Feedback from GPs, through interviews and structured written feedback, reported successful patient identification facilitated by the finder tool. One pilot GP stated the ‘finder tool was excellent and the decisional support was educational’. Feedback indicated that the divisions of intensification options in terms of glycaemic, blood pressure and lipid-lowering medications were clear and useful. All GPs thought that the initial step, of inserting information from the EHR, could be enabled by the practice nurse, allowing the GP to review this information and to assess the treatment intensification options from the CDSS in the second step. For some patients, it was noted the biggest issue was not a pharmacological, clinical or intensification issue; the GPs reported that the reasons for poor control related to ‘logistics’ and ‘an educational and compliance deficit which is not easily fixed with a structured six-month review’. Using DECIDE was also felt to be very quick, which was positive.

We used the results of the non-randomised feasibility study to modify processes in the next phase of the DECIDE intervention (the pilot cluster RCT (cRCT)). Therapeutic intensification actions were deemed not possible in approximately one third of patients, due to complex social reasons. Other strategies or actions were suggested, including referral to a community-based diabetes nurse specialist, asking for more frequent reviews and contacts with the patient and addressing addiction or frailty issues. These non-pharmacological ‘actions’ were deemed important to explore and document, prior to considering therapeutic intensification options. The non-randomised feasibility study raised the issue of whether the study should include patients with elevated BP, but with controlled HBA1c, as was done in the non-randomised feasibility study. Based on the pilot results, we decided to target only patients with HbA1c > 70 mmol/mol, as only a small number of patients had both raised BP and HbA1c and including patients with very elevated BP would increase our sample size requirement significantly for the pilot cRCT. We also identified additional data to be collected at follow-up, including consultation visitation rate and frequency of review at hospital and with community diabetes nurse specialists. Table 3 outlines the major changes made to the intervention based upon the results of the non-randomised feasibility study.

**Table 3 Tab3:** Summary of DECIDE intervention changes

Pilot component	Issue identified in non-randomised feasibility study	Change for future pilot cluster randomised controlled trial
DECIDE finder tool	Extension of utilisation to other electronic health records (EHRs) (beyond the Socrates EHR)	A bespoke Finder Function to enable practices utilising other EHRs was developed.
DECIDE CDSS and treatment escalations options	The three domains of suggested intensification options (glycaemic, anti-hypertensive and lipid-lowering medications) were appropriate, and the CDSS was deemed useful to prompt GPs on what evidence-based intensification options were available.	Not applicable.
Non-pharmacological options	Therapeutic intensification actions were deemed not possible in approximately one third of patients, due to complex social reasons.	The DECIDE intervention actions were comprised of three intensification options for glycaemic, BP and lipid-lowering medications. A forth option—providing options of non-pharmacological actions—was added to the intervention. Examples of non-pharmacological actions included referral to a community-based diabetes nurse specialist, asking for more frequent reviews and contacts with the patient or calling the patient in for another review to discuss compliance.
Follow-up of patients	Some patients with poor control were found to have significant care needs, which would require more frequent review.	An increase in the frequency of structured visits for these persons, through individualised reviews, was recommended. Though this is a contractual matter for the GPs concerned in terms of the provision of diabetes care, the DECIDE intervention was modified to enable multiple reviews—not just one review every 6 months.
Introductory educational information on the DECIDE website, in the educational videos and DECIDE practice folder	The educational information in the DECIDE folder was deemed useful.	Some minor additions to this folder, to include the above information, were added.

## Methods/Design

### Objectives of study

The primary aim of the pilot cRCT is to test the feasibility of a complex intervention that will identify T2DM patients in Irish primary care who have poor glycaemic control and support general practitioner (GP) treatment escalation where appropriate, targeting clinical inertia in physicians. The protocol outlines the pilot cRCT, which incorporates a planned process evaluation that will record GP decision-making processes and a description of an exploratory health economic analysis that will be conducted alongside the pilot cRCT. The pilot cRCT will also inform the conduct and sample size of a definitive trial using formal continuation criteria [37].

### Study design

The next phase of the DECIDE study will be conducted through a two-arm pilot cRCT, incorporating a process evaluation and exploratory economic analysis. A cluster design will be used to reduce contamination between the arms of the trial as the intervention targets GPs. It will be conducted using the CONSORT statement, extended for use in cluster RCTs [37]. The study has been registered at http://www.isrctn.com/ISRCTN69498919.

### Setting

The intervention will take place in Irish General Practice, including practices affiliated with the HRB Primary Care Clinical Trials Network Ireland (CTNI) (http://primarycaretrials.ie), in practices using one of two EHRs (Socrates and Health One) across Ireland. We will include both single-handed GPs and group practices.

### Population

GPs will be the target of the intervention and will be the unit of randomisation (the clusters).

Patients with poorly controlled T2DM will be targeted by the GP with the DECIDE intervention. All included patients must have a diagnosis of T2DM, identified by the finder tools in the EHR (discussed above). They must be aged over 18 years and less than 75, as there is less evidence about treatment intensification in patients aged above 75 years. However, patients with both a HbA1c > 70 mmol/mol and a BP > 150/ 95 mmHg will be recruited initially to the study, followed by those with an elevated HbA1c if the total number of patients with both risk factors poorly controlled is less than ten, followed by those with just elevated BP. Not all patients will be suitable for treatment intensification, and individual decisions on treatment changes will be made and recorded by each patient’s GP.

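### The protocol says the pilot targets only patients with HbA1c > 70 mmol/mol, yet its recruitment rule admits BP-only patients; if practices reach that tier, the HbA1c comparison is likely to be diluted and the stated 80% power need not hold

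*Protocol article*

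**What the plan says.** Four places in the protocol article define the patients.

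- **Development of the DECIDE study and non-randomised feasibility study.** The authors ask whether patients with raised BP but controlled HbA1c should be included, as they were in the feasibility study. The answer is "we decided to target only patients with HbA1c > 70 mmol/mol". Two reasons are given: few patients had both factors raised, and "including patients with very elevated BP would increase our sample size requirement significantly for the pilot cRCT".
- **Objectives of study.** The intervention is to "identify T2DM patients in Irish primary care who have poor glycaemic control". BP is not part of the aim.
- **Population.** Recruitment runs in three tiers per practice: both factors raised; then raised HbA1c, if fewer than ten have both; "followed by those with just elevated BP".
- **Abstract, Methods/Design.** Poor control is "defined as HbA1c > 70 mmol/mol and/or BP > 150/95".

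Three other sections decide what follows from this. Outcome measures names HbA1c as a primary outcome beside the feasibility measures. Sample size assumes a mean baseline HbA1c of 91.1 mmol/mol (SD 16.7), a reduction of 10 mmol/mol, ICC 0.027, 80% power and 10% loss, giving 14 practices of 10 patients. Data analysis compares HbA1c by intention to treat across all randomised practices and patients, adjusted for baseline HbA1c and the minimisation factors, with no restriction on baseline HbA1c.

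**The concern.** A practice running the finder tool cannot obey both an HbA1c-only rule and a rule that tops up with BP-only patients. This is not superseded text: the decision reported in the feasibility section is about this pilot.

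The conflict reaches the primary patient outcome. A BP-only patient enters with HbA1c no higher than 70 mmol/mol, so there is less room for the assumed fall of 10 mmol/mol than in a patient near 91. The Discussion adds that the study does not seek aggressive reductions in people with moderate control. Each such patient is therefore likely to pull the average HbA1c effect towards zero, and their share would vary from practice to practice.

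Two later decisions draw on the HbA1c result. The pilot is to inform the size of a definitive trial, and potential effect on glycaemic control is one of the continuation criteria. Success in recruiting patients is another, and it is hard to judge while the eligible patient is defined in two ways.

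**Working it through.** **Inputs from Sample size:** difference 10 mmol/mol, SD 16.7, ICC 0.027, power 80%, loss 10%, 10 patients per practice. **Assumed, because not stated:** two-sided 5% (in line with the planned 95% confidence intervals) and equal allocation, so 7 practices per arm.

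**Step 1: reproduce the 140.**
- Per arm without clustering: 2 × (16.7 × (1.960 + 0.842) / 10)² = 43.8, so 44.
- Design effect: 1 + 9 × 0.027 = 1.243. Then 44 × 1.243 = 54.7, so 55.
- Loss: 55 / 0.9 = 61.1, so 62.
- In practices of ten: 7 per arm, 14 in all, 140 patients.

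The plan's figure reproduces if every patient can show the 10 mmol/mol effect.

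**Step 2: power of that design.** With 9 analysed per practice, SE = 16.7 × √(2 × (1 + 8 × 0.027) / (7 × 9)) = 3.28. Power for a difference of 10 is 80% with a t reference on 12 df and 86% with the normal approximation. The document does not say which was used, so both are carried forward.

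**Step 3: dilution.** Let f be the BP-only share and assume no HbA1c effect in those patients. The average effect is 10 × (1 − f). SD is held at 16.7.

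| BP-only share | Average effect | Power (t, 12 df) | Power (normal) |
|---|---|---|---|
| 0% | 10 | 80% | 86% |
| 10% | 9 | 71% | 78% |
| 20% | 8 | 61% | 68% |
| 30% | 7 | 50% | 57% |

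On the normal approximation, power passes below 80% at a share of about 8%.

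**Step 4: partial effect.** If BP-only patients show half the effect, the average is 10 × (1 − f/2), that is 9.5, 9 and 8.5 at 10%, 20% and 30%. Power is 76%, 71% and 66% (t) or 83%, 78% and 74% (normal).

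**Step 5: the planned baseline adjustment.** Take 20% BP-only with no effect. Assume their baseline is 55 (SD 8) and that baseline and follow-up correlate at r within each group.
- Within-group variance: w = 0.8 × 16.7² + 0.2 × 8² = 235.9.
- Between-group variance: b = 0.2 × 0.8 × (91.1 − 55)² = 208.5.
- Residual variance after linear adjustment: (w + b) − (r·w + b)² / (w + b).
- Residual SD for r = 0.3, 0.5, 0.7: 16.4, 14.3, 11.4.
- Power for an average effect of 8 (t): 63%, 74%, 90%.
- An all-HbA1c sample under the same adjustment has residual SD 16.7 × √(1 − r²) and power for 10 of 83%, 90%, 97%.

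Adjustment removes most of the added spread. The remaining gap comes from the smaller average effect.

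**Step 6: is the third tier plausible?** The 37 feasibility patients averaged 83.9 mmol/mol (SD 30.8), against the 91.1 (SD 16.7) used for sizing. Suppose 91.1 describes the raised-HbA1c patients, which is an inference, and controlled patients averaged 50 to 65, which is assumed. The controlled share is then (91.1 − 83.9) / (91.1 − 50) = 18% to (91.1 − 83.9) / (91.1 − 65) = 28%. Feasibility practices sampled 15 patients by a different rule, so this gives scale only, not a forecast.

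**The case against.** The other side has several sound points.

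- **The loss is conditional.** BP-only patients come last, and only where a practice cannot find ten with raised HbA1c. The document gives no expected share. A reader might infer that the HbA1c estimate will be diluted; the text supports only that it can be.
- **Zero effect is the extreme case.** The Rationale section mentions HbA1c below 58 mmol/mol as an example of guideline control. A BP-only patient between 58 and 70 is above that, so it does not follow that such patients have nothing to gain glycaemically. Step 4 shows the milder case.
- **Baseline adjustment is planned.** A reader might widen the SD for the mixture of patients and report a much lower unadjusted power. That is not the analysis described; Step 5 is closer to it.
- **Empty places.** A reader might infer that leaving places unfilled beats filling them. At 20% empty (7.2 analysed per practice, SE 3.59) power is 72% (t), against 61% when they are filled with zero-effect patients but 71% at half effect. The ranking rests on the assumption.
- **The mixed population may be intended.** The abstract's background describes the intervention as addressing glycaemic and BP control, and BP is a secondary outcome. If a definitive trial kept the and/or rule, a mixed estimate would be the relevant one.
- **This is a pilot.** Its aim is feasibility, its sample size is called provisional, and its continuation criteria centre on feasibility.

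These points limit the size and urgency of the finding. None of them reconciles the eligibility statements, and the authors' own reason for restricting to HbA1c was the sample size.

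**Conclusion.** The contradiction is explicit and unresolved: the feasibility section and the objectives limit the pilot to raised HbA1c, while the Population section and the abstract do not. If practices reach the third tier, the average HbA1c effect is likely to be diluted, and the sizing, which reproduces for patients who can all show a 10 mmol/mol effect, need not deliver 80% power. The size of the loss runs from nil, if that tier is never used, to the Step 3 figures if it is used and BP-only patients show no HbA1c effect. Those figures rest on 7 v 7 practices, 9 analysed each, ICC 0.027 and SD 16.7. Baseline adjustment improves precision but cannot restore the average effect.

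The documents do not support saying that the stated power is wrong as it stands, because neither the share of BP-only patients nor their HbA1c response is given. For a feasibility-led pilot, this is something that should be fixed rather than a fatal flaw.

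**What to change.** Reconcile the abstract and the Population section with the feasibility section and the objectives, so that one eligibility rule applies everywhere.

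If the BP-only tier is kept:

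- define the primary HbA1c analysis set by baseline HbA1c > 70 mmol/mol recorded before allocation, and say plainly that for this outcome the intention-to-treat comparison covers all randomised patients meeting that criterion;
- report BP-only patients separately;
- state in Sample size that the calculation applies to the raised-HbA1c patients only, or restate the power for the mixed population with the assumed BP-only share and effect.

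The cost is wording in the abstract and in the Population, Sample size and Data analysis sections. Data collection already places baseline data before allocation, so no new measurement is needed. The downside is that some practices may contribute fewer than ten patients to the HbA1c analysis.
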